## Abstract

**Background:**

Falls are one of the most common medical complications post-stroke. Physical exercise, particularly exercise that challenges balance, reduces the risk of falls among healthy and frail older adults. However, exercise has not proven effective for preventing falls post-stroke. Falls ultimately occur when an individual fails to recover from a loss of balance. Thus, training to specifically improve reactive balance control could prevent falls. Perturbation training aims to improve reactive balance control by repeatedly exposing participants to postural perturbations. There is emerging evidence that perturbation training reduces fall rates among individuals with neurological conditions, such as Parkinson disease. The primary aim of this work is to determine if perturbation-based balance training can reduce occurrence of falls in daily life among individuals with chronic stroke. Secondary objectives are to determine the effect of perturbation training on balance confidence and activity restriction, and functional balance and mobility.

**Methods/design:**

Individuals with chronic stroke will be recruited. Participants will be randomly assigned to one of two groups: 1) perturbation training, or 2) ‘traditional’ balance training. Perturbation training will involve both manual perturbations (e.g., a push or pull from a physiotherapist), and rapid voluntary movements to cause a loss of balance. Training will occur twice per week for 6 weeks. Participants will record falls and activity for 12 months following completion of the training program. Standardized clinical tools will be used to assess functional balance and mobility, and balance confidence before and after training.

**Discussion:**

Falls are a significant problem for those with stroke. Despite the large body of work demonstrating effective interventions, such as exercise, for preventing falls in other populations, there is little evidence for interventions that prevent falls post-stroke. The proposed study will investigate a novel and promising intervention: perturbation training. If effective, this training has the potential to not only prevent falls, but to also improve safe independent mobility and engagement in daily activities for those with stroke.

**Trial registration:**

Current Controlled Trials: ISRCTN05434601.

## Background

Stroke is the leading cause of adult disability, and frequent falling is one of the most common medical complications post-stroke [1–3], representing significant healthcare costs. Remaining active after stroke is essential to recovery, maintaining quality of life, and reducing secondary stroke risk [4]. However, impaired postural control is associated with a high incidence of falls, reduced willingness to walk independently, and reduced overall activity [5, 6]. Balance control challenges not only elevate falls risk, but also lead to fear of falling [7] and are important determinants in reduced overall activity and community integration [8].

Previous research shows the essential role for reactive balance control in maintaining balance and mobility [9]. While falls can be initiated by external factors (e.g. slippery floor or nudge) [10], the capacity to recapture balance and prevent falling is fundamentally determined by the effectiveness of balance reactions. Fixed support reactions maintain balance without a change in the base of support (e.g. ankle and hip movements) and can be useful for defending against small postural perturbations [9, 11]. However, it is change-in-support reactions, which involve rapid stepping and grasping movements, that are ultimately essential to prevent falling [12]. Records of naturally-occurring falls and near falls reveal the importance of reactive stepping [13, 14], and that this is not a reaction reserved solely for the most potent postural perturbations [12, 15].

Reactive stepping is characterized by: 1) extremely rapid onset and movement speed [16, 17]; 2) amplitude and trajectory scaled to the degree of instability [12]; and 3) ability to accommodate environmental circumstances [18, 19]. These characteristics put tremendous demands on those with stroke, making the control of such reactions difficult [20–25]. Impaired limb control that delays execution of compensatory steps, or dyscoordination that makes foot placement or weight bearing difficult, leads to increased falls risk [24, 26, 27] and elevated fear and anxiety.

Despite control challenges associated with executing reactive steps, individuals with impaired balance control are increasingly dependent on these stepping responses because they are the last option to prevent falling. Because stroke survivors are at a high risk of falls, it is essential to develop approaches to re-train compensatory stepping after stroke. There is compelling evidence that physical exercise prevents falls among older adults [28]; however, no exercise intervention has effectively reduced risk of falls among individuals with stroke [29, 30]. More specific exercise, that is, perturbation training involving repeated exposure to applied balance disturbances, is necessary to achieve improvements in the control of fast reactive movements [22, 31–34]. Perturbation training is an emerging and promising treatment strategy for preventing falls [35]. The novelty of perturbation training is in the focus on speed of processing and execution of limb movements, as well as rapid restabilization; this differs from ‘traditional’ balance training programs using voluntary movements that allow participants to control speed. Such training is specific to the demands of balance recovery reactions to prevent a fall following a ‘real life’ loss of balance.

The primary objective of this study is to determine if a novel perturbation-based training program focused on improving reactive stepping in individuals with chronic stroke will reduce the risk for falls in the community. Secondary objectives are to determine the effect of perturbation training on balance confidence and activity restriction, and functional balance and mobility. Our primary hypothesis is that individuals with chronic stroke who complete perturbation training will be less likely to experience a fall up to 12-months following completion of the program, compared to individuals who complete a ‘traditional’ balance training program (control group). Our secondary hypothesis is that, compared to individuals in the control group, individuals with stroke who complete the perturbation training program will show: increased balance confidence; increased participation in daily activities in the year following completion of the program; and greater gains in functional balance and mobility.

## Methods

### Trial design

This is a multi-site single-blind randomized controlled trial. Research activities will take place in two centres: 1) Toronto Rehabilitation Institute – University Centre site; and 2) Sunnybrook Health Sciences Centre. Individuals with chronic stroke will be recruited and randomly assigned to one of two groups: 1) perturbation training or 2) ‘traditional’ balance training (control). Participants will record falls, activity, and participation for 12 months following completion of the training program. Functional balance and mobility, and balance confidence will be assessed before and immediately after training, 6-months after the initial training, and at the end of the 12-month follow-up (Fig. 1).

**Fig. 1 Fig1:**
[figure not shown]
Study design flowchart. Following initial screening and consent, participants will undergo an initial assessment to confirm eligibility and facilitate group allocation. Eligible participants will be randomly assigned to either perturbation training or the control group. Immediately following completion of the training period, participants will repeat assessment of functional balance and mobility and balance confidence. Participants will then complete 12 months of regular falls and activity reporting. Participants will receive ‘booster’ training sessions 3 and 9 months after the initial training period. An interim follow-up assessment and final follow-up assessment will occur 6 and 12 months following the initial training period

### Participants

Community-dwelling individuals with chronic stroke (>6 months post-stroke) who are ≥50 years will be recruited. All participants will be able to stand independently without upper-limb support for >30 s and able to tolerate at least 10 postural perturbations while wearing a safety harness.

The following exclusion criteria will be applied: >2.1 m tall and/or weighing >150 kg (limits of the safety harness system); other neurological conditions that could affect balance control (e.g. Parkinson’s disease); lower extremity amputation; cognitive, language, or communication impairments affecting understanding instructions; recent (last 6 months) significant illness, injury or surgery; severe osteoporosis, defined by diagnosis of osteoporosis with fracture; poorly controlled diabetes or hypertension; contraindications to physical exercise, as identified using the Physical Activity Readiness Questionnaire [36]; currently attending in- or out-patient physiotherapy or other exercise targeting balance and mobility; and/or received perturbation training during formal rehabilitation in the 1 year prior to enrolment.

Eligible participants who have enrolled in research volunteer databases at participating sites will be invited to participate. Additionally, advertisements will be placed in the community (e.g., posters placed in participating sites, magazine advertisements, online advertisements) requesting volunteers for the study. Interested individuals will initially complete a telephone screening to determine eligibility. If the volunteer meets the criteria for the study, s/he will be scheduled to come to the site for an initial assessment. Prior to the initial assessment, the site research assistant will explain the study procedures again and will obtain written informed consent to participate.

To confirm eligibility, participants will initially complete an assessment of reactive balance control using a lean-and-release postural perturbation of stance (Fig. 2; [37]). Two conditions will be completed: usual response, and encouraged use (5 trials in each condition). Participants will wear a harness attached to an overhead support and research staff will stand close to them to assist in the event of a failure to recover balance. Trials will be video-recorded for observational analysis.

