#### Group 2: perturbation training

The perturbation training program is grounded in motor learning principles of practice variability, practice order, feedback, guidance, instruction, and focus of attention, and in exercise physiology principles of overload, adaptation, progression, individualization, and specificity [31]. The initial assessment of reactive balance control will be used to identify participant-specific impairments in the control of reactive stepping; these impairments will then be targeted in the training program. A variety of tasks will be included to induce external or internal postural perturbations. External perturbations will be caused by forces outside the participants’ control (e.g., a push or pull from the physiotherapist). Internal perturbations are caused when the participant fails to control the centre of mass-base of support relationship during voluntary movement; ‘agility’ tasks, such as kicking a soccer ball, can be used to induce internal perturbations. Each session will include a 5−10 min warm-up, voluntary tasks that may induce internal perturbations, voluntary tasks combined with up to 60 external perturbations, and a 5−10 min cool-down. The number of repetitions is similar to previous studies [31, 32, 42], and our pilot testing indicates that individuals with sub-acute stroke can tolerate up to 30 perturbations in a 20 min session [22]. The task difficulty will be set such that participants will require an upper extremity response or external assistance (i.e., from the overhead harness or physiotherapist) or take more than 2 steps to regain stability approximately 50 % of the time. The progression in voluntary tasks occurs on a continuum from stable to mobile, and from predictable to unpredictable [49]. Additionally, progression occurs by increasing the magnitude of the external perturbation, or imposing sensory or environmental challenges. Examples of some of the training tasks are included in Table 1; a detailed training manual is available from the authors.

**Table 1 Tab1:** Examples of voluntary tasks used in the perturbation training program

Week	Task type	Definition	Examples
1	Stable	Participants do not move their feet.	• Standing with eyes closed.
			• Shifting weight left/right or forward/back.
2-3	Quasi-mobile	Participants move their feet but remain ‘on the spot’.	• Rapid stepping forward and back.
			• ‘Walking’ in place.
4−5	Mobile	Participants move around the room.	• Walking forward or backward.

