
### Statistical analysis and sample size

Negative binomial regression will be used to compare fall rates between the two groups and logistic regression will be used to compare the proportion of fallers between the two groups. If the groups differ on prognostic factors (e.g., stroke severity) or on physical activity during the follow-up period (i.e., PASIPD scores) then multiple negative binomial/logistic regression will be used. Intent-to-treat analysis will be used; all individuals with some falls-monitoring data will be included in the analysis. Survival analysis may be considered if a large number of individuals do not complete the entire 12-month follow-up. Exploratory per-protocol analysis and/or comparison of fall rates between those who return for the ‘booster’ training sessions and those who do not may also be conducted. Repeated-measures analysis of variance, with group-by-time interaction, will be used to evaluate the effect of the interventions on secondary outcome measures (e.g., functional balance measures, balance confidence). The interaction effect will reveal if there is a greater pre- to post-training improvement in the perturbation training group compared to the control group.

The target sample size has been estimated using a formula for negative binomial regression described elsewhere [78]. Assuming a rate of falls in the control group of 1.75 per person per year [27], a reduction in rate of falling of 46 % in the perturbation training group [35], mean follow-up time of 11 months per person (i.e., some participants will be lost to follow-up before 12 months), level of significance (α) of 0.05, and power (1-β) of 0.8, we estimate that 37 participants per group will be required to show significant effects. From previous studies [32, 79], we expect that ~20 % of individuals will withdraw prior to completing the intervention. While many of these individuals will be willing to complete the 12-month falls monitoring period and could be included in intent-to-treat analysis, we conservatively assume that 20 % of individuals will withdraw from the study. Therefore, we will aim to recruit at least 46 participants per group (i.e., 92 participants total).

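### The one-year washout covers perturbation training only in formal rehabilitation, so volunteers recently trained in research or community programmes could enter either arm and may dilute the contrast

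*Protocol article*

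**What the plan says.** All of the eligibility and recruitment text is in the Participants section of the protocol article.

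- **Washout.** A person is excluded who "received perturbation training during formal rehabilitation in the 1 year prior to enrolment".
- **Neighbouring exercise criterion.** A person is excluded who is "currently attending in- or out-patient physiotherapy or other exercise targeting balance and mobility". This reaches beyond formal care, but only for exercise under way at the time.
- **Recruitment.** There are two routes: "Eligible participants who have enrolled in research volunteer databases at participating sites will be invited to participate", and "Additionally, advertisements will be placed in the community". Eligibility is first checked by telephone.

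Elsewhere, the Background section hypothesises that the benefit of perturbation training lasts up to 12 months after the programme. Group allocation and blinding describes concealed randomisation, stratified by site and by baseline failures in the reactive balance test.

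**The concern.** By including a washout, the protocol treats perturbation training in the past year as a reason not to enrol someone. The restriction to formal rehabilitation then makes the answer depend on where the training was given. Training in a clinic last month excludes a person; the same training in a research study or community programme last month does not. No reason is given for the distinction. The setting left out matters because one of the two recruitment routes is a pool of research volunteers. The exercise criterion does not close the gap, because it stops at current attendance.

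On the trial's own hypothesis of a lasting effect, a control participant who was recently trained may already have part of the benefit under test. That lowers the comparator fall rate and moves the rate ratio towards 1. It could also narrow the differences in the balance outcomes. Eligibility cannot be repaired after randomisation without departing from the planned intent-to-treat analysis.

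**Working it through.** **Inputs from Statistical analysis and sample size.** "Assuming a rate of falls in the control group of 1.75 per person per year"; "a reduction in rate of falling of 46 % in the perturbation training group", so the planned rate ratio is 0.54; "mean follow-up time of 11 months per person", so t = 11/12 = 0.917 year; α = 0.05, power 0.80. Sidedness and the dispersion parameter k are not stated.

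**Step 1: the plan's own figure.** For negative binomial counts,

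n per group = (z₀.₉₇₅ + z₀.₈₀)² × [1/(t·r₀) + 1/(t·r₁) + 2k] / (ln RR)²

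With r₀ = 1.75, r₁ = 1.75 × 0.54 = 0.945 and k = 0:

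- 1/(0.917 × 1.75) + 1/(0.917 × 0.945) = 0.623 + 1.154 = 1.778
- (1.960 + 0.842)² = 7.849; (ln 0.54)² = 0.380
- n = 7.849 × 1.778 / 0.380 = 36.8, that is 37 as stated (two-sided, k near 0)
- 37/0.8 = 46.25, in line with the stated 46

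This point disputes neither figure.

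**Step 2: dilution (assumed model).** A share f of each arm was trained within the year outside formal rehabilitation. In the control arm these people keep a fraction c of the 46% reduction. In the perturbation arm everyone ends at the planned rate of 0.945, whether trained before or not, so only the control rate changes:

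control rate = 1.75 × (1 − 0.46·c·f); observable RR = 0.54 / (1 − 0.46·c·f)

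For example, with c = 1 and f = 10%: 0.54 / 0.954 = 0.566, a reduction of 43.4%.

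**Step 3: power with 37 analysed per group and k = 0.** Power = Φ(|ln RR| / SE − 1.96), with SE² = [1/(t·r_control) + 1/(t·0.945)] / 37.

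| Share f | Full carry-over (c = 1): RR, reduction | Power | Half carry-over (c = 0.5): RR, reduction | Power |
|---|---|---|---|---|
| 0% | 0.540, 46.0% | 80% | 0.540, 46.0% | 80% |
| 5% | 0.553, 44.7% | 77% | 0.546, 45.4% | 79% |
| 10% | 0.566, 43.4% | 73% | 0.553, 44.7% | 77% |
| 20% | 0.595, 40.5% | 64% | 0.566, 43.4% | 73% |

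In numbers of people, 5% of 37 is about 2 per arm, 10% about 4 and 20% about 7.

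**Step 4: dependence on k.** The reductions in the table do not depend on k; the power figures do. With k = 1 (assumed), power at 37 per group starts at 49% and falls to 46%, 43% and 36% for f = 5%, 10% and 20% with full carry-over. The choice of k therefore matters more to power than this dilution does, but it is a separate matter.

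**The case against.** **No exposed group is shown.** The document does not say that anyone in the databases has had perturbation training, how many, or how recently. The Background section calls the approach novel and emerging, which does not suggest that many people have been trained outside clinics. This stands: the contamination is possible, not demonstrated.

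**The pilot work does not fill that gap.** A reader might infer a ready pool of trained volunteers from Group 2: perturbation training, where "our pilot testing indicates that individuals with sub-acute stroke can tolerate up to 30 perturbations in a 20 min session". The sentence is about tolerance. It gives no course of training, setting, date or link to the databases. If the work took place in rehabilitation within the year, the existing criterion already covers it; if it is older than a year, even a widened criterion would not apply. The point does not rest on it.

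**Randomisation protects the comparison.** A reader might infer that trained people would gather in the control arm and bias the result. Allocation is concealed, so they are expected in both arms in equal proportion. Stratification by baseline failures also helps to balance reactive balance between arms. The comparison stays valid for the people enrolled. What randomisation and stratification do not restore is the lost contrast.

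**Full carry-over is an upper bound.** Trial interventions says only that booster sessions may help to retain some benefit. Someone trained one month before enrolment would be about 1 + 1.5 = 2.5 months past that training when falls monitoring starts after the 6-week programme, and 14.5 months past it at the end. This stands, and it is why half carry-over is shown beside it.

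**An article condenses the protocol.** The telephone screening questions may well be in the full document. But the washout criterion itself is stated here, and the point concerns its stated scope.

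**Conclusion.** The point holds as a minor one. As written, the washout lets in people who had perturbation training within the year in a research study or community programme, while one recruitment route is a database of research volunteers. The possible consequence is a smaller contrast and some lost power. The documents do not support a claim of bias between arms or of contamination known to exist.

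Under full carry-over the observable reduction falls from 46% to 44.7%, 43.4% or 40.5% for shares of 5%, 10% or 20%. With 37 analysed per group and almost no overdispersion, power falls from 80% to 77–79%, 73–77% or 64–73% respectively (full to half carry-over). The share and the carry-over are both assumptions. The loss is small unless about 10% or more were previously trained and retained most of the benefit. That the washout is meant to keep recently trained people out is inferred from the criterion, since the article gives no rationale for it.

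**What to change.** In the Participants section, remove the restriction to formal rehabilitation, so that perturbation training in any setting (rehabilitation, research study or community programme) within one year before enrolment excludes. Add one question on this to the telephone screening. No stated figure changes: the sample size stays at 37 analysed and 46 recruited per group. The cost is one line of eligibility text, one screening question and a few volunteers who become ineligible. The change has to be in place before participants are randomised.

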**Fig. 2 Fig2:**
[figure not shown]
Lean-and-release postural perturbation. The participant leans forward so that approximately 10 % of body weight is supported by a cable attached to her back. At an unexpected time, the cable is released, causing the participant to start falling forward; a reactive step is required to regain stability. The research assistant stands close to provide assistance if the participant is unable to regain stability by stepping. A safety harness attached to an overhead support frame is worn, which prevents a fall to the floor. Panel **a** shows the ‘usual response’ condition where the participant is free to respond naturally. Panel **b** shows the ‘encouraged use’ condition; the preferred stepping limb (typically the non-paretic limb) is blocked, preventing step initiation with that limb and forcing use of the opposite limb to regain stability. (The individual shown is not a research participant. Consent was obtained for publication of the picture in this manuscript)

As this is a longitudinal study, participants may be lost to follow-up. To help keep track of participants, we will request contact information of a friend or family member (‘alternative contact’). The alternative contact will only be contacted to obtain information about the whereabouts of a research participant if we are unable to contact him/her after multiple attempts.

